### Statistical analysis

All analyses will be performed in the ITT-population (intention-to-treat). Instead of the patients, the GPs and their practices will be randomized into clusters. Hence, for the primary analysis, a mixed model with repeated measurements will be adapted at the HbA1c-values of the follow-up. This model includes three levels of hierarchy: GP/practice, patients in the GP’s practice, repeated measurements on the patient-side. Any unstructured covariance matrix will be allowed/admitted for the repeated measurements. First the initial value will be the covariate of the model. An additional covariate on the patient- or GP-level will already be included in the primary analysis, because maldistributions are more typical for cluster-randomized studies than for individually randomized studies. They will be selected right after the patient recruitment has been finalised - considering the baseline values, but without knowing the follow-up values. The coefficient test, comparing the baseline-adjusted final HbA1c-values between the randomized groups, will be performed within the primary analysis. We will use the direct Maximum-Likelihood as the statistical estimation procedure, which results in unbiased estimated values under the missing-at-random-assumption. Alternatively, sensitivity analyses such as last-observation-carried-forward (LOCF) and other worst-case scenarios will be determined. A difference of 0,5% (HbA1c) between the groups will be considered clinically relevant. Depending on their measurement scales the secondary endpoints will be analyzed with analogue models up to the primary endpoint.

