### Recruitment

#### GPs

The responsible KV^a^ in every study area provides a list of all GPs taking part in primary care. By sending invitation letters, scientific staff in the three study centres performs different waves of recruitment consecutively until the target number is reached. Each study centre recruits 20 GPs from its catchment area for the study (total = 60).

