### Randomisation

After the baseline data collection the GPs will be randomized into intervention- and control group.

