### Quality assurance (safety board, gender-specific aspects, interference factors)

The data safety monitoring board (DSMB) will consist of three scientists (one biostatistician and two GPs), who are not associated with the participating institutions performing the study. Based on the interims-analyses of the outcomes the DSMB can vote for a discontinuation of the study.

Some studies refer to gender-specific risk factors and consequences of diabetes [58-60]. To take these into account we will perform analyses stratified by gender. On the level of data analysis we will test whether the intervention reaches the poorly regulated patients with diabetes mellitus type 2 and to what extent. Gender-specific differences might also exist and be relevant for the empowerment-potential.

Confounding variables will primarily be controlled by the randomization. Unevenly allocated characteristics of patients or doctors will be included in the primary assessment model, since the maldistribution of cluster-randomized studies cannot be ignored and therefore needs to be taken into consideration. Potential disturbance variables, which occur after the inclusion will, on the one hand, be minimized by standardizing the study process and handed over essential parts of the documentation to the study assistants. On the other hand, quality assurance measures will be performed within the course of the study. No information regarding the specific hypothesis of the study and the relevance of primary/secondary endpoints will be given to patients and GPs.

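### Study centre, a design factor known before randomisation, has no fixed place in the primary model; the cost is some precision, or a conservative test, not validity

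*Protocol article*

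**What the plan says.** Recruitment (GPs) makes centre part of the design: "Each study centre recruits 20 GPs from its catchment area for the study (total = 60"). The sample-size section names the three centres. Randomisation is described in one sentence, "After the baseline data collection the GPs will be randomized into intervention- and control group", which neither states nor excludes stratification by centre.

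Statistical analysis sets out the primary model in some detail:

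- Structure: "This model includes three levels of hierarchy", namely GP or practice, patient within practice, and repeated measurement within patient.
- Fixed covariate: "First the initial value will be the covariate of the model", that is, baseline HbA1c.
- Further adjustment: "An additional covariate on the patient- or GP-level will already be included in the primary analysis", justified by the greater risk of uneven distribution in cluster-randomised trials.
- Timing: "They will be selected right after the patient recruitment has been finalised - considering the baseline values, but without knowing the follow-up values".

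The Quality assurance section repeats the principle: "Unevenly allocated characteristics of patients or doctors will be included in the primary assessment model".

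None of these sections names study centre as a term in the model.

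**The concern.** Centre is known for every GP before allocation, and GPs are recruited in equal numbers by centre. Such a factor is normally put in the model because of the design, not because of what the baseline data show. Here its only route into the model is a rule driven by observed imbalance. That rule serves centre poorly in either case the article leaves open:

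- **Allocation within centre.** Centre is balanced by construction, so a rule that looks for imbalance has no reason to select it. Yet this is where omission makes the reported standard error too large, because between-centre variation is counted in the GP-level error although it no longer contributes to the group difference.
- **Allocation without regard to centre.** Moderate imbalance is likely, and whether centre is adjusted for depends on a judgement after baseline for which the article gives no threshold.

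At stake are precision and one avoidable data-driven choice in the primary model.

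**Working it through.** **Inputs from the sample-size section:** ICC 0.1, 10 evaluable patients per GP, 54 GPs after practice dropout (27 per arm), difference 0.5. **Assumed, because the article gives no between-centre variance:** a share s of the GP-level variance remaining after baseline adjustment lies between centres, with s = 10%, 20% or 30%. Two-sided 5% is also assumed.

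**1. The plan's own inflation.** 1 + (10 - 1) x 0.1 = 1.9, as stated. 286 x 1.9 = 543.4, about 54 GPs with 10 patients each; 54/0.9 = 60; 60 x 13 = 780. These steps reproduce.

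**2. Variance of a GP mean, with total variance set to 1.** GP part 0.1 plus patient part 0.9/10 = 0.09, together 0.19 (which is 1.9/10). With centre as a fixed effect the GP part becomes 0.1 x (1 - s), so

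variance ratio = (0.1 x (1 - s) + 0.09) / 0.19.

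| s | Variance ratio | SE ratio (square root) | Cut in SE from adding centre |
|---|---|---|---|
| 0 | 1.000 | 1.000 | 0% |
| 10% | 0.18/0.19 = 0.947 | 0.973 | 2.7% |
| 20% | 0.17/0.19 = 0.895 | 0.946 | 5.4% |
| 30% | 0.16/0.19 = 0.842 | 0.918 | 8.2% |

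Read the other way, the standard error without centre is 1/0.973 to 1/0.918 times what it need be, about 3-9% larger.

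**3. Allocation within centre, centre omitted.** The true standard error is the reported one times the SE ratio, so the actual level is 2 x P(Z > 1.96 / SE ratio):

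- s = 10%: 1.96/0.973 = 2.014, level 4.4%
- s = 20%: 1.96/0.946 = 2.072, level 3.8%
- s = 30%: 1.96/0.918 = 2.136, level 3.3%

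A simulated GP-level comparison of 60 GPs allocated 10:10 within centre agrees: 4.4%, 3.8% and 3.3%.

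**4. Allocation without regard to centre, centre omitted.** With 30:30 over three centres of 20, the exact probability that at least one centre splits 12:8 or worse is 0.68, and 13:7 or worse 0.35. In simulation the type I error without centre nevertheless stays at about 5% (5.0-5.1% for s = 10-30%; 4.8-5.0% in a separate run for shares of 10-50%). The imbalance is chance variation that the GP-level error already covers.

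**5. Power.** SE = sqrt(2 x SD^2 x (0.1 x (1 - s) + 0.09) / 27).

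- SD 0.9, as stated: SE 0.107 without centre, 0.104 to 0.098 with centre for s = 10-30%. Power for a difference of 0.5 is above 99% throughout.
- SD 1.5: SE 0.178 without centre, 0.173 to 0.163 with centre. Power rises from 80% to 82%, 84% and 86% for s = 10%, 20% and 30%.

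SD 1.5 is shown because it gives 142-143 per arm, matching the stated 143, whereas SD 0.9 gives only 51-52. That mismatch is a separate matter; here it only means that the power figures at SD 0.9 may be too favourable.

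**The case against.** The best defence is that this is a condensed article. Whether centre is a stratum and a model term is often left to the full protocol or analysis plan, and a list of hierarchical levels does not exclude a fixed effect. This stands in part: centre is not ruled out, and the full documents may name it. But the article does more than stay silent. It states a principle for choosing covariates, and that principle would miss centre when allocation is balanced within it.

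A second defence is that an uneven centre split could be picked up as an unevenly distributed characteristic. That is possible, but it is not assured, and it does not help under balanced allocation.

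Third, baseline HbA1c is already a covariate and would absorb much of any stable regional difference. This stands, and it is why the share s must be read as what remains after baseline adjustment. The documents give no reason to expect it to be large.

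A reader might infer from the frequent 12:8 or 13:7 splits that the comparison is biased or the test anti-conservative. The documents do not support that. Those splits presuppose unstratified allocation, which the article does not state; they are not probabilities of a wrong conclusion; and under such allocation the type I error stays at about 5%.

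**Conclusion.** The point holds as a minor efficiency improvement. The primary model as described gives centre no assured place, and the imbalance rule is the wrong way to decide on a known design factor. The consequence is lost precision or, if allocation is within centre, a conservative test. Treatment-effect bias and an inflated type I error do not follow.

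The size rests wholly on the assumed centre share. At 10-30% of the residual GP-level variance, the standard error could be cut by about 3-8%, and a within-centre allocation analysed without centre would test at about 4.4-3.3% instead of 5%. Near zero, the loss is negligible. The calculation also takes the plan's ICC of 0.1 and 10 patients per GP as given and treats the analysis as a comparison of GP means at one time point.

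**What to change.** Add to Statistical analysis: *Study centre (three levels) is included as a fixed effect in the primary model and in the analogue models for secondary endpoints, whether or not it is balanced between the groups.* A fixed effect is preferable because three centres are too few to estimate a random centre variance well.

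State in Randomisation whether allocation is stratified by centre. If it is not, and GPs have not yet been randomised, allocate the 20 GPs of each centre 10:10.

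The cost is a sentence in each section and two of about 52 between-cluster degrees of freedom (54 GPs less two groups). No new data are needed, since centre is known for every GP. The change also removes one data-driven choice from the primary model.

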### Sample size/power calculation

Assuming a residual standard deviation of 0.9 a case number of 2x 143 (=286) patients is required to realize a randomized study on the patient-side to show a difference in the HbA1c of 0.5 with a statistical power of 80%. Due to the design of the study (cluster-randomized study with an intervention on the GPs-side) the resulting cluster-effects according to the case number have to be taken into account. The derived factor will be 1.9 assuming an ICC of 0.1 and an average cluster-size of 10. Assuming an average dropout rate of approx. 20%, it is necessary to recruit at least 54 GPs, who treat 13 patients each in order to assure no less than 10 eligible patients per GP [45]. The recruitment of 60 practices is required assuming a practice-drop-out rate of 10%. In order to achieve the calculated sample size (n = 780 patients) the study was designed as a multi-centred study with study centres in Rostock, Düsseldorf and Witten (Institute of General Practice at Rostock University, Institute of General Practice at the Heinrich-Heine University in Düsseldorf, Institute of General Practice and Family Medicine at the University of Witten/Herdecke).

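### The primary model is to be fitted by maximum likelihood with about 54 to 60 randomised GPs; read literally, this slightly understates the standard error of the group difference (minor)

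*Protocol article*

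**What the plan says.** All of the following is in the protocol article.

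- **Estimator and its justification** (Statistical analysis): "We will use the direct Maximum-Likelihood as the statistical estimation procedure". The reason given is that the estimates are unbiased if data are missing at random. The next sentence there turns to LOCF and worst-case scenarios as sensitivity analyses.
- **Model** (Statistical analysis): "This model includes three levels of hierarchy: GP/practice, patients in the GP’s practice, repeated measurements on the patient-side". For the visits: "Any unstructured covariance matrix will be allowed/admitted for the repeated measurements".
- **Primary test** (Statistical analysis): "The coefficient test, comparing the baseline-adjusted final HbA1c-values between the randomized groups, will be performed within the primary analysis". No z or t reference and no degrees-of-freedom rule is given, and the article states no significance level.
- **Covariates**: besides the baseline value, "An additional covariate on the patient- or GP-level will already be included in the primary analysis" (Statistical analysis). Quality assurance says, in the plural: "Unevenly allocated characteristics of patients or doctors will be included in the primary assessment model". No number is fixed.
- **Clusters** (Sample size/power calculation): "it is necessary to recruit at least 54 GPs", raised to 60 for 10% practice dropout, with an ICC of 0.1 and an average cluster size of 10.

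**The concern.** Treatment varies only between GPs, so the precision of the group comparison is governed by how much GP means vary. ML estimates that variation without deducting the degrees of freedom used by the intercept, the group effect and any GP-level covariates. With several hundred clusters this would not matter. With 54 to 60 it gives a small bias that always goes in the anti-conservative direction.

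The reason given for ML does not cover this. Unbiasedness under missing at random concerns the fixed effects. It does not extend to the ML variance components, which set the standard error and the p-value. REML has the same missing-data justification, so that argument gives no ground for preferring ML.

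The covariate plan adds to the effect, because each GP-level covariate uses another cluster degree of freedom that ML ignores. The secondary endpoints are to be analysed with analogous models, so the choice carries over to them.

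**Working it through.** **The plan's own figures.** The article states no type I error to reproduce. Its cluster count can be followed from the 286 patients onward: 286 × 1.9 = 543.4; 543.4 / 10 ≈ 54 GPs; 54 / 0.9 = 60; 60 × 13 = 780. How the 286 was reached is a separate question and does not enter here.

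**Inputs from the article.** J = 54 or 60 GPs; ICC 0.1; 10 patients per GP.

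**Assumptions.** Two-sided 5% test; total variance scaled to 1, so GP variance 0.10 and remainder 0.90; equal cluster sizes in the closed form; p = 0, 1 or 3 GP-level covariates.

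**Step 1: bias of the between-GP variance under ML.** The variance of a GP mean is 0.10 + 0.90/10 = 0.19. ML shrinks it by the fraction (2+p)/J, and the whole shortfall falls on the GP component. The relative bias is therefore (2+p)/J × 0.19/0.10. For J = 54:

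- p = 0: 2/54 × 1.9 = 7.0%
- p = 1: 3/54 × 1.9 = 10.6%
- p = 3: 5/54 × 1.9 = 17.6%

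In simulation the ML estimate averaged 0.93, 0.90 and 0.82 of the true value, and 0.94 in a four-visit model with p = 0. REML averaged 1.00.

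**Step 2: effect on the standard error.** ML/REML ratio r = sqrt((J−2−p)/J). For J = 54:

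- p = 0: sqrt(52/54) = 0.981, about 2% too small
- p = 1: sqrt(51/54) = 0.972, about 3% too small
- p = 3: sqrt(49/54) = 0.953, about 5% too small

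**Step 3: type I error.** With d = J−2−p and critical value c, the size is 2 × P(t_d > c × r). Here c = 1.96 for a z reference, or the 97.5% point of t_d for a t reference. Example for J = 54, p = 0: with z, 1.96 × 0.981 = 1.923, giving 6.0%; with t, 2.007 × 0.981 = 1.969, giving 5.4%. For REML, r = 1.

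| GPs | GP-level covariates | ML, z | ML, t | REML, z | REML, t |
|---|---|---|---|---|---|
| 54 | 0 | 6.0% | 5.4% | 5.5% | 5.0% |
| 54 | 1 | 6.2% | 5.7% | 5.5% | 5.0% |
| 54 | 3 | 6.8% | 6.1% | 5.6% | 5.0% |
| 60 | 0 | 5.9% | 5.4% | 5.5% | 5.0% |
| 60 | 1 | 6.1% | 5.6% | 5.5% | 5.0% |
| 60 | 3 | 6.6% | 6.0% | 5.5% | 5.0% |

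**Step 4: simulation check.** The first row is a three-level model with four visits, unstructured covariance and an assumed within-patient correlation of 0.5 (8,000 runs). The others are single-visit models (12,000 runs each). The simulation standard error is about 0.2-0.3 points.

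| Scenario | ML, z | ML, t | REML, z | REML, t |
|---|---|---|---|---|
| 54 × 10, four visits, p = 0 | 6.0% | 5.5% | 5.7% | 5.2% |
| 54 × 10, p = 0 | 6.4% | 5.7% | 5.9% | 5.2% |
| 54 × 10, p = 1 | 6.3% | 5.8% | 5.6% | 5.0% |
| 54 × 10, p = 3 | 7.0% | 6.3% | 5.8% | 5.1% |
| 60 × 13, p = 1 | 5.8% | 5.2% | 5.1% | 4.8% |

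For 54 GPs and one GP-level covariate, unequal cluster sizes or an ICC of 0.05 or 0.2 moved ML with z only within 6.3-6.5%.

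**Step 5: how much is due to ML.** At 54 GPs and p = 0, REML with z already runs at 5.5%. About half of the one-point excess of ML with z therefore comes from z. At p = 3, REML with z gives 5.6% against 6.8% for ML with z, so ML is then the larger part.

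**The case against.** The strongest reply is that the sentence is about missing data. It is justified by missing at random and followed by LOCF and worst-case analyses, so it may mean only a likelihood analysis of all observed values without imputation. REML is neither named nor excluded, and the unbiasedness statement is true for the fixed effects. This reading is plausible and cannot be ruled out. The sentence nevertheless names maximum likelihood as the estimation procedure, and an analysis that followed it literally would carry the bias. The same edit serves either reading.

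A second reply is that ML versus REML and the degrees-of-freedom method usually belong in the SAP, which is not shown. That holds for the degrees of freedom, and their absence is not counted as an error here. It holds less for the estimator, which the article does name.

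A reader might infer that the article fixes a primary test running at 6-7% and that ML is the cause. The documents do not support that. The figure needs a z reference and a 5% level, neither of which is stated. Its upper end also needs about three GP-level covariates, while the article gives no number and allows patient-level ones. With a t reference and no or one such covariate, the closed-form size is 5.4-5.7%.

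**Conclusion.** The point holds as a minor one. Taken literally as ML, with 54 GPs and no or one GP-level covariate, the between-GP variance is underestimated by roughly 6-10% and the standard error of the group difference by about 2-3% (about 5% with three). Under an assumed two-sided 5% level, the type I error is about 5.4-5.7% with t on cluster degrees of freedom and 6.0-6.3% with z. With three GP-level covariates it is 6.1-6.8%. With 60 GPs it is slightly lower.

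The direction and mechanism are firm. The size depends on the reference distribution, the level and the number of GP-level covariates, none of which the article fixes, and on whether ML was meant as opposed to REML. It does not show that the primary test as planned fails to hold its error rate.

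**What to change.** Replace the estimation sentence with, for example: *The model will be estimated by restricted maximum likelihood (REML), using all observed follow-up values under the missing-at-random assumption, with Kenward-Roger or Satterthwaite degrees of freedom for the group coefficient.* Apply the same to those secondary endpoints that are analysed with analogous linear mixed models.

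The cost is one sentence and a software option, with no extra patients or data. Against literal ML with 54 GPs, the confidence interval widens by 1/r − 1: about 2% with no GP-level covariate, 3% with one and 5% with three. If z had been intended, moving to t adds about 2.4-2.5% (for example 2.007/1.96 = 1.024).

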### Quality assurance (safety board, gender-specific aspects, interference factors)

The data safety monitoring board (DSMB) will consist of three scientists (one biostatistician and two GPs), who are not associated with the participating institutions performing the study. Based on the interims-analyses of the outcomes the DSMB can vote for a discontinuation of the study.

Some studies refer to gender-specific risk factors and consequences of diabetes [58-60]. To take these into account we will perform analyses stratified by gender. On the level of data analysis we will test whether the intervention reaches the poorly regulated patients with diabetes mellitus type 2 and to what extent. Gender-specific differences might also exist and be relevant for the empowerment-potential.

Confounding variables will primarily be controlled by the randomization. Unevenly allocated characteristics of patients or doctors will be included in the primary assessment model, since the maldistribution of cluster-randomized studies cannot be ignored and therefore needs to be taken into consideration. Potential disturbance variables, which occur after the inclusion will, on the one hand, be minimized by standardizing the study process and handed over essential parts of the documentation to the study assistants. On the other hand, quality assurance measures will be performed within the course of the study. No information regarding the specific hypothesis of the study and the relevance of primary/secondary endpoints will be given to patients and GPs.

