## Methods/Design

### Design of the study

An educative intervention will be tested under real conditions in a primary care setting within the framework of a cluster-randomized controlled study. First the participants (GPs and their patients) are recruited and baseline data will be recorded. This is followed by the randomisation of the participating GPs into intervention- and control group. Then data will be recorded at four different measure points (6,12,18,24 months after baseline). GPs allocated to the control group will not take part in any intervention program, but will treat their patients as usual. Patients of those GPs randomized into the intervention group will receive substantial empowerment. It has to be taken into consideration that the recruitment of the GPs and their patients for the study already presents a first intervention, because of the higher attention paid to the problem, by patients and GPs.

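### Covariates enter the primary model because they look unevenly allocated: the stated timing does not fit that rule, and imbalance is the wrong criterion

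*Protocol article*

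**What the plan says.** All references are to the Protocol article.

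- **Fixed covariate** (Statistical analysis): baseline HbA1c is always in the model: "First the initial value will be the covariate of the model".
- **Extra covariate and its reason** (Statistical analysis): "An additional covariate on the patient- or GP-level will already be included in the primary analysis, because maldistributions are more typical" of cluster-randomised trials.
- **When it is chosen** (Statistical analysis): "They will be selected right after the patient recruitment has been finalised - considering the baseline values, but without knowing the follow-up values". The text moves from one covariate to a plural.
- **The criterion** (Quality assurance): "Unevenly allocated characteristics of patients or doctors will be included in the primary assessment model". No limit on number is given here.
- **Order of events** (Design of the study): recruitment and baseline recording come first, and then "This is followed by the randomisation of the participating GPs into intervention- and control group". The Randomisation section agrees: "After the baseline data collection the GPs will be randomized into intervention- and control group".

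**The concern.** A characteristic can be unevenly allocated only once there are arms. Covariates are to be chosen as soon as recruitment ends, and randomisation comes after recruitment and baseline. Read literally, the criterion has nothing to act on at the time set for it. If the choice is instead made just after randomisation, it can be carried out, but the content of the primary model is then decided by people who can see the allocation.

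The criterion is weak in either case. With randomised arms, a baseline difference is a chance event that carries no information on whether the factor predicts HbA1c. The rule can therefore admit irrelevant factors that happen to differ, using up cluster-level degrees of freedom, and leave out prognostic factors that happen to balance. What is at stake is the precision of the primary comparison and how firmly its model is fixed in advance.

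**Working it through.** **1. Timing.** Two orders are possible, and the documents do not say which holds.
- Selection before randomisation: no between-arm difference exists, so the Quality assurance rule cannot be applied. No imbalance-driven power loss can arise either.
- Selection after randomisation but before follow-up data: the rule can be applied, with allocation visible.

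**2. The plan's own sample size, to find where power stands.** Inputs from Sample size/power calculation: difference 0.5, residual SD 0.9, power 80%, ICC 0.1, cluster size 10, 54 practices analysed. Alpha is not stated; 0.05 two-sided is assumed.
- n per arm = 2 × (1.96 + 0.84)² × SD² / difference².
- At 0.5: 2 × 7.849 × 0.81 / 0.25 = 50.9, so 51. The plan has: "Assuming a residual standard deviation of 0.9 a case number of 2x 143 (=286) patients is required".
- At 0.3: 2 × 7.849 × 0.81 / 0.09 = 141.3, so 142; the t-test version gives 142.2, so 143.

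The 143 thus corresponds to 0.3 with SD 0.9, or equivalently 0.5 with SD 1.5. That mismatch is a separate matter. Here it means that two power settings have to be shown.
- Cluster-mean variance = 0.81 × (0.1 + 0.9/10) = 0.1539.
- SE of the difference = √(4 × 0.1539 / 54) = 0.107.
- Power at 0.3: Φ(0.3/0.107 − 1.96), about 80%. At 0.5: about 99.7%.

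**3. How often the rule fires.** Under Data collection, 7 GP items and 15 patient items besides HbA1c can be counted, 22 in all. If they are treated as independent and screened at p<0.05 (both assumptions), the chance of at least one imbalance is 1 − 0.95²² = 68%. With 6 candidates it is 1 − 0.95⁶ = 26%.

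**4. Power of the rule.** Simulation of 54 cluster means (27 per arm), variance 0.1539, analysed by ANCOVA on cluster means, with independent normal candidates and 8,000 runs per cell. One candidate has correlation r with the cluster mean and the rest have none. SD 0.9 is taken as already adjusted for baseline HbA1c. *Fixed* always includes the one candidate; *selected* includes every candidate with imbalance p<0.05.

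| Difference | r | Candidates | Unadjusted | Fixed | Selected | Fixed − selected |
|---|---|---|---|---|---|---|
| 0.3 | 0 | 6 | 78.4% | 77.8% | 77.2% | 0.6 |
| 0.3 | 0 | 22 | 78.4% | 77.6% | 74.0% | 3.6 |
| 0.3 | 0.4 | 6 | 79.1% | 84.6% | 78.4% | 6.2 |
| 0.3 | 0.4 | 22 | 79.0% | 84.7% | 74.8% | 9.9 |
| 0.3 | 0.6 | 6 | 79.5% | 93.1% | 79.6% | 13.5 |
| 0.3 | 0.6 | 22 | 78.8% | 93.0% | 75.8% | 17.2 |
| 0.5 | 0 to 0.6 | 6 | 99.4–99.6% | 99.4–100% | 99.3–99.7% | 0.1–0.3 |
| 0.5 | 0 to 0.6 | 22 | 99.5–99.7% | 99.6–100% | 99.0–99.2% | 0.6–0.9 |

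Monte Carlo error is about half a point per cell near 80% power. Repeat runs moved the ends of the 0.3 range by about a point, to 18 at the top, so it should be read as roughly 6 to 18. With 22 candidates, selection falls below even the unadjusted analysis at 0.3; with 6 the two are about equal.

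**5. Type I error.** At zero difference, the selected rule rejected in 3.9 to 5.4% of runs.

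**The case against.** The strongest reply has four parts.

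- **The timing may be only loose wording.** No section orders covariate selection relative to randomisation. A choice made just after allocation and before any follow-up value is compatible with the text. This stands. A reader might infer that the plan selects by imbalance before arms exist and also loses power through it. The two exclude each other, so the documents support only the either/or.
- **The power loss is not general.** It needs a prognostic factor beyond baseline HbA1c, and the documents give no such strength. At the stated difference and SD every rule has about 99 to 100% power. A fixed set can also cost power: in a similar simulation at 0.3, six fixed covariates with no prognostic value gave 73.4% against 77.1% for imbalance selection. All of this stands, so the loss must be stated conditionally.
- **No false-positive problem is shown.** A reader might suspect that choosing the model with allocation visible inflates type I error. The simulations do not show this, and blindness to follow-up values is a real safeguard against choosing by outcome.
- **Silence is not error.** It is tempting to add that study centre is missing from the model, that allocation is unstratified, or that small-sample degrees of freedom are absent. A protocol article may leave these to the full protocol or SAP, and they are not part of this point. The same goes for a candidate list and an imbalance threshold.

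The reply does not answer the core. The article states a criterion for the primary model, that criterion does not fit the stated timing, and it does not track what makes adjustment useful.

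**Conclusion.** The point holds as an inconsistency and an inefficient selection rule in the primary analysis. It is not a threat to validity. The Statistical analysis and Quality assurance sections must be reconciled on when covariates are chosen and by what criterion.

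If the imbalance rule is applied after allocation, its cost against one truly prognostic fixed covariate is:
- roughly 6 to 18 points of power at a true difference of 0.3, with r of 0.4 to 0.6;
- about 0 to 4 points at 0.3 if the covariate has no prognostic value;
- under 1 point at the stated 0.5 with SD 0.9.

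These figures assume two-sided alpha 0.05, 6 to 22 independent candidates, a p<0.05 threshold, equal clusters, and a cluster-mean analysis in place of the full repeated-measures model. The 0.3 is inferred from the stated 143 per arm and does not appear in the article. If selection comes before allocation, there is no such loss, but the Quality assurance sentence cannot be carried out.

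**What to change.** - Delete the imbalance criterion from Quality assurance, and drop maldistribution as the ground for choosing covariates in Statistical analysis.
- Name, before allocation, a short set of primary-model covariates on prognostic grounds from data already collected at T0: baseline HbA1c plus a few, for example study centre, patient age, gender and time since diagnosis. State that the set is final before randomisation.
- Present models adjusted for observed imbalances only as sensitivity analyses.

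The cost is a few sentences in the protocol or SAP; no new data are needed. There are two small downsides. A chance imbalance in an unlisted factor will show only in a sensitivity analysis. Fixed covariates without prognostic value cost a little power, which is why the set should be short.
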